**Methods:**

Two hundred subjects (100 reference, 50 AF, and 50 HF) are being invited to participate in wearing a Fitbit fitness tracker for 3 months. Interested volunteers are sent a questionnaire to determine their health, in particular cardiovascular health. Volunteers without any (history of) serious illness are assigned to the reference group. Participants with AF and HF are recruited in the Haga teaching hospital in The Hague, The Netherlands.

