## Methods

### Study design and data collection

ME-TIME (registered at ClinicalTrials.gov; ID: NCT05802563) is designed as an observational cohort study consisting of 3 data subject groups, as depicted in Figure 1. The first group consists of patients with systolic heart failure (HF group); the second group consists of patients with documented atrial fibrillation (AF group); and the third group, serving as a reference, consists of healthy volunteers. The rationale for creating distinct AF and HF groups comes from their unique pathophysiological characteristics. Consequently, heart rate patterns that are indicative of these diseases might also be different. The HF group consists of 50 study participants with systolic heart failure, defined as a left ventricular ejection fraction <35% without documented atrial fibrillation. The AF group consists of 50 patients with documented atrial fibrillation (paroxysmal, persistent, or permanent) without systolic heart failure. Ejection fractions will be assessed from echocardiograms that are made within 1 year of inclusion, and if this is not available an echocardiogram will be performed. The reference group consists of 100 participants without any prior medical history and without medication use. Potential study subjects that meet any of the following criteria will be excluded from participation in this study: age <18 years, age >85 years, recent pulmonary venous antrum isolation (<1 year), kidney or liver failure, known systemic active inflammatory disease, impaired mental state, inability to use a fitness tracker or mobile phone, impaired cognition, and inability to understand the study protocol.

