**Figure 1 fig1:**

Data analysis pipeline for the ME-TIME study. Included participants (image 1) are given a smartwatch (image 2), which is connected to our data acquisition and storage platform (image 3). The resulting data are then preprocessed (image 4) and put into the data-efficient machine learning model (image 5). AF = atrial fibrillation group; HF = heart failure group; Ref = reference group.

Patients will be asked by their treating physician if they may be approached by an investigator to inform them about the study and potential participation. Healthy participants are recruited through local advertising. Anyone that is interested will then receive an information brochure and informed consent form. At least 2 days after the patient’s receipt of the brochure, the research team will call the patient to schedule an appointment. During this visit, the patient submits the signed consent form and will undergo an ECG and blood pressure measurement that will be analyzed by an experienced cardiologist ([name]). Participants can use their own Fitbit and are otherwise provided with a Fitbit Inspire 2 or Fitbit Charge 5 smartwatch. The device type is assigned to a participant at random to prevent device sampling bias. This will also help to investigate the effect of device type on the performance of the final model. A Fitbit account will be created for all participants which will be connected to a custom-built data platform using the Google Cloud Platform. Our platform features a data portal for research staff to easily register or deregister participants by authorizing a connection to their Fitbit data. Data are extracted daily from Fitbits until the observation period ends and can be analyzed either in the cloud or locally.

All participants will be asked to fill out a survey regarding their health. All participants are monitored for a period of 3 months. After written consent from the 200 subjects, heart rate, step counter, and sleep time series data are extracted from the data platform. Clinical metadata such as age, height, weight, blood pressure at baseline, health survey, and medication use are saved in the Castor (Ciwit BV, Amsterdam, The Netherlands) electronic database.

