### Data characteristics and preparation

The data first undergoes a process involving resampling and artifact removal. In our experience with Fitbit smartwatches, the heart rate is nonuniformly sampled, with a prevalent rate of 0.2 Hz. Therefore, the heart rate is resampled to once per 5 seconds. The step counter is sampled once per minute.

Artifacts involving samples with numerous consecutive constant values are removed, if more than 12 consecutive constant values (equivalent to 1 minute of heart rate samples) are detected. This 1-minute threshold was chosen based on visual inspection, which revealed that heart rate patterns typically occur in the order of minutes, often spanning 10–20 minutes. For sequences with fewer than 12 consecutive missing values, linear interpolation is applied. From the cleaned time series, smaller segments, denoted as windows, are extracted and employed as input for a machine learning model. This process involves a sliding window and windows containing time gaps are excluded. Windows have 2 design considerations: the window size, which determines the number of samples within a window and defines its dimensionality, and the stride, which establishes the step size dictating the shift between windows.

Although the cardiovascular condition of each subject is known, it is unknown in which specific windows these conditions manifest themselves. This is owing to the paroxysmal nature of atrial fibrillation and the variable symptoms of heart failure, which can be influenced by factors like medication adjustments, dietary changes, and the disease’s progressive course. In other words, the subject label is known, but the individual window labels are unknown. This is visually represented in Figure 2a, where the subject label is depicted by the blue/red colors and the unknown window labels are indicated by black dotted lines.

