### Study characteristics

So far, 62 of the 200 envisioned subjects have been included and data from 22 subjects (15 healthy, 7 AF) have been extracted successfully from the data platform for preliminary analysis (Table 1).

**Table 1 tbl1:** Characteristics of preliminary study participants as of May 2022

Characteristic	Ref	HF	AF
Participants, n	25	15	22
Age, y			
18–39	16	1	0
40–54	3	3	2
55–64	5	5	3
65+	1	6	17
Sex			
Male	12	12	15
Female	13	3	7
BMI			
18.5–24.9	14	3	7
25–29.9	6	6	8
30+	5	6	7
Diabetes			
Yes	0	5	4
No	25	10	18
Smoking			
Yes	0	6	5
No	25	9	17
Hypertension			
Yes	2	8	15
No	23	7	7
Device			
Charge 5	23	8	12
Inspire 2	2	7	10

AF = atrial fibrillation group; BMI = body mass index; HF = heart failure group; Ref = reference group.

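### The reference group is drug-free by rule and the patient groups are not, so patient-versus-reference performance cannot be read as detection of AF or HF, and neither test set can show this

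*Protocol article*

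**What the plan says.** The section on study design and data collection defines the reference arm thus: "The reference group consists of 100 participants without any prior medical history and without medication use". The disease arms are defined by the disease and by absence of the other disease. For AF: "The AF group consists of 50 patients with documented atrial fibrillation (paroxysmal, persistent, or permanent) without systolic heart failure". For HF the criterion is "defined as a left ventricular ejection fraction <35% without documented atrial fibrillation". Neither definition limits medication, and apart from the other condition and the exclusions common to all groups, neither limits comorbidity. Patients are approached through their treating physician, and reference subjects through local advertising.

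The Abstract (Methods) gives a different reference rule: "Volunteers without any (history of) serious illness are assigned to the reference group". It sets no condition on medication.

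Medication and health data are collected: "Clinical metadata such as age, height, weight, blood pressure at baseline, health survey, and medication use are saved" in the study database. The model is to use heart rate, step count and sleep. The section on algorithm validation stratifies the folds by class. It then names two test sets. The external one holds unseen subjects, 20% of the total, with equal numbers per class. The internal one holds the last 20% of each series from subjects already used. Device type is the only covariate whose effect on model performance is to be examined.

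**The concern.** A classifier trained on this contrast is rewarded for any signal that differs between the groups, whether it comes from the disease, from its treatment, or from age and risk factors. With no medicated reference subject there is no overlap on medication, so no later adjustment can separate drug from disease within patient-versus-reference. Good sensitivity and specificity would then be open to more than one explanation.

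This matters because of the uses the article names. The Introduction aims at early detection, and the Results and Discussion speak of ruling out heart disease in people with symptoms. People with undiagnosed disease need not be on treatment for it. Symptomatic people without heart disease need not resemble volunteers with no history and no drugs. Neither sensitivity nor specificity from this contrast can be assumed to carry over to them.

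**Working it through.** The article states no performance target or sample-size calculation, so there is no figure of its own to reproduce. As an input check, the Table 1 age bands add up to the group sizes: reference 16+3+5+1 = 25, HF 1+3+5+6 = 15, AF 0+2+3+17 = 22, total 62.

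**Step 1: what the rule alone allows.** Let m be the share of patients on any medication (not given). Under the Methods rule the share in the reference group is 0. A perfect detector of medication use, blind to disease, would have specificity 100%, sensitivity m and balanced accuracy (1 + m)/2. With the planned 100 patients and 100 reference subjects, its overall accuracy is (100 + 100m)/200, the same value.

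| Assumed m | Balanced accuracy |
|---|---|
| 50% | 75% |
| 70% | 85% |
| 90% | 95% |
| 100% | 100% |

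These are ceilings. The model sees medication only through whatever effect it has on heart rate, steps or sleep.

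**Step 2: imbalance seen so far (Table 1).**

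| Factor | AF (n=22) | HF (n=15) | Reference (n=25) |
|---|---|---|---|
| Age 65+ | 17 (77.3%) | 6 (40.0%) | 1 (4.0%) |
| Hypertension | 15 (68.2%) | 8 (53.3%) | 2 (8.0%) |
| Diabetes | 4 (18.2%) | 5 (33.3%) | 0 |
| Smoking | 5 (22.7%) | 6 (40.0%) | 0 |

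Age is the largest imbalance for AF. Ranking subjects by age band alone (ties counted as one half) gives an AUC of 0.94 for AF versus reference and 0.84 for HF versus reference. Age 65+ as a rule for AF versus reference has sensitivity 17/22 = 77.3%, specificity 24/25 = 96.0% and balanced accuracy 86.6%. Hypertension alone has 15/22 = 68.2%, 23/25 = 92.0% and 80.1% (Fisher exact p = 0.00004). With AF and HF pooled, diabetes is 9/37 against 0/25 (p = 0.008) and smoking 11/37 against 0/25 (p = 0.002).

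**Step 3: can the validation detect this?** The external set is a random 20% of the same cohort, so its reference subjects meet the same rule and its patients come from the same source. The internal set reuses the same subjects. Class stratification keeps the contrast constant across folds. A model that reads treatment or age would do as well in these sets as one that reads disease. The external set has 0.20 × 200 = 40 subjects, or 40/3 ≈ 13 per class. If m were 80% to 100%, each disease class would contain about 13 × 0.20 = 2.6 down to 0 untreated patients, too few to examine there.

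**Step 4: the reference rule itself.** The Methods require no medical history of any kind, the Abstract requires no serious illness, and Table 1 lists 2 of 25 reference subjects with hypertension. The Methods rule and Table 1 fit together only if hypertension there means something other than history, such as a reading at the visit. The article does not say. If the Abstract's rule is the one applied, some reference subjects may take medication, and the lack of overlap would be less than complete.

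**The case against.** The strongest reply is that this is a condensed article. It says the metadata are stored, not that they will go unused, and a metadata baseline or a report by drug use is commonly left to the analysis plan. The Discussion also promises to explore ways of mitigating inter-subject variability, though it names no covariate. This stands in part: silence about the metadata is not an error. The inclusion rule, however, is fixed here, and no analysis plan can create medicated reference subjects.

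A reader might go further in four ways that the documents do not support.

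- **That the model does detect treatment or risk factors.** Table 1 shows that the groups differ. It does not show that the wearable signals carry those differences. The phrase "factors like medication adjustments, dietary changes" concerns the variable symptoms of heart failure, not drug effects on heart rate. That treatment affects heart rate is an assumption here.
- **That nearly all patients are treated.** No share is given, hence the range in the working.
- **That hypertension alone beats the pilot model.** Table 2 gives that model sensitivity 11/25 = 44.0% and specificity 33/40 = 82.5%. Those are weeks, and the preliminary analysis drew on 22 subjects (15 healthy, 7 AF). The hypertension figures count 47 enrolled subjects, so the two are not comparable.
- **That the wearable has value only for its gain over a model that includes medication.** Such a model is near-perfect because of the inclusion rule if most patients are treated. It would leave little room for gain even for a device that truly detects AF.

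It is also fair to say that reanalysis cannot repair the missing overlap. The remedy limits what is concluded and adds contrasts that are less affected.

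**Conclusion.** The point holds as a consequence of the design. Under the Methods rule, patient-versus-reference performance mixes disease with drug status by construction, and with age and comorbidity as enrolled so far. Neither planned test set can show how much of the performance each explains. The imbalance in Table 1 is measured, from 62 of the 200 planned subjects. The medication part is structural, and its size is unknown because neither the treated share nor its effect on the signals is reported. The conclusion rests on the Methods rule being the one applied, and it weakens for medication if the Abstract's rule was used.

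The reference rule does not confound AF versus HF. That contrast is not free of imbalance, though: age 65+ is 17/22 against 6/15, and drug use in the two groups is not given.

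**What to change.** 1. Reconcile the reference-group rule in the Methods with the Abstract and with the two hypertensive reference subjects in Table 1, and state which rule was applied at enrolment.
2. On the same folds and the same external test subjects, fit a metadata-only comparator with age, sex, BMI, hypertension, diabetes and smoking, **without** medication. Report the wearable model beside it and added to it, with subject-level bootstrap intervals.
3. Report AF-versus-HF discrimination as the contrast that the reference rule does not confound, with drug use and age shown by group.
4. Report sensitivity by use of heart-rate-affecting drugs from the pooled cross-validation predictions, since the external set has only about 13 subjects per class.
5. Word the patient-versus-reference conclusion as separating treated patients from drug-free volunteers, with the treated share reported. Do not claim early detection, or rule-out in symptomatic people, from that contrast.

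The cost is a little more analysis of data already held, and performance that may look less favourable. No further recruitment is needed.

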**Figure 1 fig1:**

Data analysis pipeline for the ME-TIME study. Included participants (image 1) are given a smartwatch (image 2), which is connected to our data acquisition and storage platform (image 3). The resulting data are then preprocessed (image 4) and put into the data-efficient machine learning model (image 5). AF = atrial fibrillation group; HF = heart failure group; Ref = reference group.

Patients will be asked by their treating physician if they may be approached by an investigator to inform them about the study and potential participation. Healthy participants are recruited through local advertising. Anyone that is interested will then receive an information brochure and informed consent form. At least 2 days after the patient’s receipt of the brochure, the research team will call the patient to schedule an appointment. During this visit, the patient submits the signed consent form and will undergo an ECG and blood pressure measurement that will be analyzed by an experienced cardiologist ([name]). Participants can use their own Fitbit and are otherwise provided with a Fitbit Inspire 2 or Fitbit Charge 5 smartwatch. The device type is assigned to a participant at random to prevent device sampling bias. This will also help to investigate the effect of device type on the performance of the final model. A Fitbit account will be created for all participants which will be connected to a custom-built data platform using the Google Cloud Platform. Our platform features a data portal for research staff to easily register or deregister participants by authorizing a connection to their Fitbit data. Data are extracted daily from Fitbits until the observation period ends and can be analyzed either in the cloud or locally.

All participants will be asked to fill out a survey regarding their health. All participants are monitored for a period of 3 months. After written consent from the 200 subjects, heart rate, step counter, and sleep time series data are extracted from the data platform. Clinical metadata such as age, height, weight, blood pressure at baseline, health survey, and medication use are saved in the Castor (Ciwit BV, Amsterdam, The Netherlands) electronic database.

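### Device type is meant to be random, but own Fitbits are allowed and the interim Table 1 shows device associated with class, which class-only stratification would not reveal

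*Protocol article*

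**What the plan says.** Under Methods, Study design and data collection, the article gives the device rule in three consecutive sentences:

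- Source of the watch: "Participants can use their own Fitbit and are otherwise provided with a Fitbit Inspire 2 or Fitbit Charge 5 smartwatch".
- Allocation: "The device type is assigned to a participant at random to prevent device sampling bias".
- Second purpose: "This will also help to investigate the effect of device type on the performance of the final model".

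The target is given in the abstract: "Two hundred subjects (100 reference, 50 AF, and 50 HF". Results, Study characteristics reports progress: "So far, 62 of the 200 envisioned subjects have been included". Table 1 splits these 62 by group, in the order Ref, HF, AF: "Participants, n 25 15 22", "Charge 5 23 8 12" and "Inspire 2 2 7 10".

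Algorithm validation stratifies the cross-validation folds by class and draws an external test set of 20% of subjects with equal numbers per class. The internal test set is the last 20% of data from subjects already used in development. Device is not mentioned in any of these steps.

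**The concern.** Random assignment is the only safeguard against device bias that the article names, and it cannot cover a watch that the participant already owns. Healthy volunteers come through local advertising and patients through their physician, so own-device use could well differ by class. The interim table then shows the association that random assignment was meant to prevent, and it runs along the healthy/diseased line that the model has to learn.

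Two things are at stake. First, if the two watch models leave different traces in the data, a model could use them as a proxy for disease. Both test sets come from the same participants, so they would carry the same association and count the shortcut as accuracy. Second, the stated study of device effect needs reference subjects on both devices to say anything useful about specificity.

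**Working it through.** **Inputs (Table 1).**

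| Group | Charge 5 | Inspire 2 | Total | Inspire 2 share |
|---|---|---|---|---|
| Ref | 23 | 2 | 25 | 8.0% |
| HF | 8 | 7 | 15 | 46.7% |
| AF | 12 | 10 | 22 | 45.5% |
| All | 43 | 19 | 62 | 30.6% |

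**Reproduction.** 23+2 = 25, 8+7 = 15, 12+10 = 22, and the total is 62, as the article states. Every participant is counted under one of the two models, so any own watches are inside these rows and cannot be told apart.

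**Association of device with class.**

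- 3×2 table: exact (Freeman-Halton) p = 0.0043. Pearson chi-square = 10.11 on 2 df, p = 0.0064. Cramér's V = √(10.11/62) = 0.40.
- Ref against patients (2/25 against 17/37): odds ratio = (17×23)/(20×2) = 391/40 = 9.8. The standard error of the log odds ratio is √(1/17+1/23+1/20+1/2), giving a 95% interval of 2.0 to 47.6. Fisher p = 0.0017.
- Ref against HF p = 0.0077; Ref against AF p = 0.0060; HF against AF p = 1.00.

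The exact tests condition on the margins, so they do not need the allocation ratio, provided it was the same for all groups.

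**Could own devices explain it?** Suppose that every own watch is a Charge 5 in the reference group, and remove k of them. With k = 10 (13/2 against 20/17) Fisher p = 0.031. With k = 11 (12/2 against 20/17) p = 0.053. So at least 11 of the 23 would have to be own devices before p exceeds 0.05. The article does not give the number.

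**Size of the possible shortcut.** The rule that Inspire 2 means patient has sensitivity 17/37 = 46% and specificity 23/25 = 92% per subject in Table 1. It was chosen after seeing the table, so it describes the present imbalance and predicts nothing about the final model.

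**If the pattern continued to 200 (an assumption).**

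- Inspire 2 would be worn by 100×2/25 = 8 Ref, 50×7/15 ≈ 23 HF and 50×10/22 ≈ 23 AF.
- The 95% half-width for a between-device difference in specificity is 1.96×√[s(1−s)(1/8+1/92)]. This is 0.29 at s = 0.80 and 0.22 at s = 0.90 (both values of s are assumed).
- With reference subjects split 50/50 it is 1.96×√[s(1−s)(1/50+1/50)] = 0.16 and 0.12.
- The external test set would hold 0.20×200 = 40 subjects, about 13 per class. Of 13 Ref subjects, 13×0.08 ≈ 1 would wear Inspire 2, and the hypergeometric chance of none is 31%.

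**If the remaining participants were allocated 1:1 within group (assuming that all take supplied devices).** There remain 200−62 = 138: 75 Ref, 35 HF and 28 AF. Expected Inspire 2 is 2+37.5 = 39.5/100 Ref, 7+17.5 = 24.5/50 HF and 10+14 = 24/50 AF. A chi-square on these expected counts gives p ≈ 0.44.

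**The case against.** Table 1 is interim, with 75 of 100 reference subjects still to come, and ordinary 1:1 allocation from here would remove most of the imbalance. That stands. It is a reason to act now, since nothing in the article says that the present pattern will change.

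A reader might infer more than the article supports:

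- **Randomisation failed.** Own watches are not separated in Table 1, and no allocation ratio is given. A ratio or supply that changed while the groups enrolled at different times could also produce the split. Silence on ratio and stratified allocation is normal in a condensed article and is no fault in itself.
- **The model learns the device.** Device is not a stated input, and no signal difference between Charge 5 and Inspire 2 is reported. The Introduction's caveat about wearable quality is general. The preparation steps (resampling, removal of constant runs, interpolation, exclusion of windows with gaps) may also remove part of any device trace. The shortcut is a risk and has not been shown.
- **The preliminary classifier in Table 2 reflects device.** Its figures are per week and rest on 15 healthy and 7 AF subjects whose device mix is not given. They cannot be set against a per-subject device rule.
- **The device effect cannot be estimated.** No cell is empty. Sensitivity can be compared between devices within HF (8 against 7) and AF (12 against 10). Specificity is imprecise, but it is identifiable.

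None of this removes the conflict between the own-device option and the random-assignment claim, or the association in the table.

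**Conclusion.** The concern holds in a limited form and should be fixed. The article claims a protection that its own-device option weakens and that its interim data do not show: odds ratio 9.8 (95% interval 2.0 to 47.6) for Inspire 2 in patients against reference, with HF and AF alike. Validation balanced on class alone would leave a device shortcut unseen. The planned look at device effect is where it might surface, and that comparison is weakest for specificity. The half-widths of 0.22 to 0.29 rest on the interim pattern continuing and on specificity between 0.80 and 0.90. The association itself rests only on Table 1. Its cause, and whether any model would exploit it, are unknown.

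**What to change.** 1. Limit the random-assignment statement to supplied devices.
2. For the remaining 138 participants, randomise supplied devices 1:1 in permuted blocks within each group (Ref, HF, AF).
3. Record whether each watch is own or supplied, report own devices separately by group, including for the 62 already enrolled, and add a sensitivity analysis without own-device users.
4. Add device to the stratification of the folds and the external test set where counts allow.
5. Report sensitivity and specificity within device, and beside them the performance of a rule that uses device alone.

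The cost is an allocation list, possibly some extra Inspire 2 watches, a small change of wording and a little more analysis. Own-device users can stay in the study and in the main test set. Some imbalance from the first 62 will remain (about 39.5% Inspire 2 in Ref against 48.5% in patients), so steps 4 and 5 are needed as well as step 2. Once enrolment closes, allocation can no longer restore balance.
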